#### CATCH Study

In a randomized, controlled trial, 299 patients with acute chest pain but normal electrocardiogram findings and troponin values were randomized to CCTA in a stable phase and 301 to standard care (Textbox 1) [24]. CCTA was performed on a 320-detector scanner with standard premedication and contrast protocols [24].

The primary purpose is to investigate whether the AI-generated label of cardiac decompensation will have an independent prognostic value to predict death and heart failure hospitalization within 3 years of follow-up. An automatic AI report of cardiac decompensation on CCTA may guide early heart failure treatment for patients with NSTE-ACS. This is beneficial, as the lung field of CCTA often is underused but can provide important complementary information about pulmonary diseases.

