### Training and Internal Validation Cohort

We extracted CT scans with accompanying radiological reports from all medical departments at the Copenhagen University Hospital–Bispebjerg and Frederiksberg Hospital, Denmark, conducted from January 1, 2016, to December 31, 2021. Consequently, 12,348 CT scans from 5111 studies of 4672 individual patients were extracted (Figure 1).

The scans originated from all medical wards ordering acute CT scans as standard diagnostic procedures. All types of CT scans (chest CT and abdominal scans, including the lungs) were included, encompassing various manufacturers, contrast-enhanced scans, noncontrast scans, low-dose protocols, and various imaging phases. Given the comprehensive inclusion of all acute chest CT examinations, the indications for these scans were broad and included assessments of chest pain, dyspnea, suspected pulmonary embolism, suspected pulmonary infection, suspected pneumothorax, or pleural effusion. We did not extract CT scans for patients aged 18 years or younger and participants in the Feasibility of Computer Tomography in Patients with Acute Decompensated Heart Failure (FACTUAL) study, as it served as a clinical validation cohort [7].

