### Target Condition Distribution

Previous studies from Denmark have reported that acute heart failure accounts for approximately 6% of medical hospital admissions among adults [19], that the incidence of pneumonia requiring hospitalization was 442 per 100,000 person years in 2003 [20], and that the incidence of pulmonary embolism requiring hospitalization occurs at a rate of 64 per 100,000 adults annually [21]. Preliminary labeling of the development dataset shows a similar distribution, with 7% to 8% positive for cardiac decompensation, while labeling for pneumonia and pulmonary embolism is still ongoing.

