### Validation of the AI Algorithm

The AI algorithms will be internally validated using the area under the curve from ROC curves and confusion matrices. Optimal thresholds for the likelihood of heart and lung diseases will be obtained from the validation cohort and defined by a true positive rate and true negative rate of 90% or greater. These thresholds will be tested for the prediction of heart and lung diseases in the validation cohorts.

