### Statistical Analyses

In each validation cohort, the default thresholds obtained from the internal validation will be used to calculate the diagnostic ability of the AI algorithm to predict the prespecified heart and lung diseases. We will, for all diagnoses, calculate odds ratios, sensitivity, specificity, positive and negative predictive values, positive and negative likelihood ratios, and area under the curve from the ROC curves.

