## Discussion

### Anticipated Findings

#### Overview

This study aims to develop and validate AI algorithms to automatically analyze chest CT scans and deliver instant feedback on the probability of dyspnea-related conditions. Our primary focus is on detecting cardiac decompensation while also laying the groundwork for assessing pneumonia and pulmonary embolism. To broadly test the algorithm, we evaluate the algorithm for cardiac decompensation in 3 different cohorts. The intended use of the algorithms is to assist in the detection of these conditions in a hospital setting, particularly in acutely admitted patients presenting with dyspnea. The algorithm is designed to support physicians, both radiologists and nonradiologists, by aiding in the early identification of critical findings while awaiting the final radiologic report. The AI model will provide interpretability through SHAP values for participant-level explanations, supported by visual inspection of segmentations and a numerical probability score for each detected disease. Its primary role will be to expedite early decision-making by highlighting relevant imaging features, potentially reducing time to diagnosis and treatment initiation. Optimizing the use of CT scans is crucial given their increasing prevalence. Currently, there is no standardized routine for describing cardiac decompensation on chest CT scans, presenting a gap that AI applications can fill.

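### The primary prognostic aim in VERDICT and CATCH names only the thresholded AI label; no analysis of the existing probability score is named beside it

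*Protocol article*

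**What the plan says.** The Methods subsection on the CATCH study states the primary purpose for the coronary CT cohorts: to find out if the "AI-generated label of cardiac decompensation" independently predicts death and heart failure hospitalization over 3 years. The predictor it names is a label.

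Two places say how a label is obtained:

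- Validation of the AI Algorithm: thresholds come from the internal validation cohort and are "defined by a true positive rate and true negative rate of 90% or greater".
- The rule under Statistical Analyses is this: "In each validation cohort, the default thresholds obtained from the internal validation will be used to calculate the diagnostic ability of the AI algorithm".

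The internal validation data are a random third of the development patients. Of these data the article says: "The scans originated from all medical wards ordering acute CT scans as standard diagnostic procedures". Preliminary labelling is "with 7% to 8% positive for cardiac decompensation".

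The target cohorts differ. In VERDICT, 1023 patients with NSTE-ACS had CCTA. In CATCH, 299 patients with chest pain but normal ECG and troponin were randomized to CCTA in a stable phase.

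A continuous output exists: the Discussion (Anticipated Findings, Overview) promises "a numerical probability score for each detected disease". The overview of the CCTA validation also states an aim to calibrate the algorithm on these scans. Strengths and Limitations describes calibration as normalization, data augmentation and cross-cohort validation. The same section says that VERDICT and CATCH have no radiological reports and mainly serve to assess prognosis.

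**The concern.** A yes/no label discards all gradation above and below the cut. It also ties the prognostic test to where the cut happens to fall in scans of a different type and in patients of a different kind. If CCTA shifts the score distribution, the share labelled positive shifts with it, and the label may isolate very few patients or far too many.

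Neither of the plan's other elements covers this. The area under the ROC curve is threshold-free, but it is listed as a diagnostic measure, and these two cohorts have no radiological reference against which to compute it. The calibration aim is not said to move the cut, and without a radiological reference there is no stated basis for resetting it to 90%/90%.

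The prognostic result is therefore the main evidence from these cohorts. If the label shows no association, the reader cannot tell a badly placed cut from an algorithm without prognostic content.

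**Working it through.** The article gives no event count, effect size, alpha, power or label-positive share for this aim, so there is no stated figure to reproduce. Its Power Calculation section concerns algorithm development.

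**Inputs from the article:** sensitivity and specificity of at least 90% (taken as exactly 90%); prevalence 7-8% in development data; 1023 + 299 = 1322 patients in the CCTA groups. **Assumed:** that 90%/90% carries over to CCTA; prevalences of 1-10% there; the two risk models below.

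**Step 1. Share labelled positive.** q = 0.9 × prev + 0.1 × (1 − prev).

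| Prevalence | q |
|---|---|
| 1% | 0.009 + 0.099 = 10.8% |
| 2% | 0.018 + 0.098 = 11.6% |
| 5% | 0.045 + 0.095 = 14.0% |
| 7.5% | 0.0675 + 0.0925 = 16.0% |

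**Step 2. Model A: normal score, log-linear hazard, small effect.** Information kept by the label = φ(c)² / [q(1 − q)], where c is the normal quantile that leaves a share q above it.

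- q = 16%: c = 0.994, φ(c) = 0.2433; 0.0592 / 0.1344 = 0.44 kept, 56% lost.
- q = 10.8%: c = 1.237, φ(c) = 0.1856; 0.0344 / 0.0963 = 0.36 kept, 64% lost.
- Even a cut at the median keeps only 64%. The loss exceeds half when fewer than about 21% are positive.

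**Step 3. Model B: a binary latent disease alone drives risk.** The score is normal with equal variance in diseased and non-diseased, separated by 2 × 1.2816 = 2.563 SD, so that one cut gives 90%/90%. Information kept = corr(label, disease)² / corr(posterior probability, disease)². At 7.5% prevalence:

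- Label: (0.0675 − 0.075 × 0.16)² / (0.075 × 0.925 × 0.16 × 0.84) = 0.00308 / 0.00932 = 0.330.
- Posterior probability, by numerical integration: 0.566.
- Ratio 0.330 / 0.566 = 0.58 kept, 42% lost.

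The label keeps 65% at 10% prevalence, 49% at 5%, 30% at 2% and 20% at 1%.

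The coding of the score matters here. In model B the logit of the probability is linear in the score. Entered as a single linear term, it has squared correlation 0.313 with disease at 7.5% prevalence, slightly below the label's 0.330. The gain in model B therefore comes only if non-linearity is allowed for.

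**Step 4. What the loss means in events (model A).** Events = (1.960 + 0.842)² / (ln 1.5)² = 48 for the score, at an assumed hazard ratio of 1.5 per SD, two-sided 5% and 80% power. Dividing by the share kept at 16% positive gives 109 for the label.

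**Step 5. Sensitivity to a shift.** If CCTA moved all scores by 0.5 SD (assumed), 16% positive would become 7% or 31%. A hazard ratio per SD does not change under such a shift.

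**The case against.** A reader might infer that the trial will use only the label. The article does not say so. The statement is one sentence of purpose, no prognostic model is specified, and nothing excludes the score. The fuller plan may include it. That stands, so the point is limited to what the article names.

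A reader might also take it as stated that the internal-validation cut governs the prognostic label. The Statistical Analyses sentence is about diagnostic ability. Carrying the cut into the prognostic analysis is the likely reading, because no other threshold rule exists, but it is not explicit. The development data also included contrast-enhanced scans, so contrast as such is not new to the model.

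A third tempting reading is that most of the information, or most of the power, is lost. No positive share or event count is given for these cohorts, and model B at 7.5% prevalence shows a loss below half. Lost information is also not the same as lost power. At 16% positive, 109 events would be 8% of 1322 patients, and the article does not allow one to say whether that number is reached in 3 years.

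The strongest objection is that the label is a legitimate target. The stated rationale is an automatic report that may guide early treatment. A flag can be useless even when the score is prognostic, and then the cut is part of what is tested. This is a good reason to keep the label. It is not a reason to leave the score out, since the probability is itself an intended output.

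**Conclusion.** The point holds in limited form. The article names a thresholded label as the predictor for its primary prognostic aim, offers one threshold rule, taken from a different scan population, and names no analysis of the score for this aim.

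The loss is 56-64% of the information at 11-16% positive in model A. In model B it is 42% at 7.5% prevalence and more than half at 5% or below. All of these figures rest on 90%/90% performance holding in CCTA, which the article does not establish, and on prevalences that it does not give.

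The firmer consequence does not depend on the risk model: a null result for the label alone cannot separate a misplaced cut from a non-prognostic algorithm. The documents do not show that the label should be demoted. They do support placing the score beside it.

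**What to change.** - Prespecify the continuous score as a prognostic analysis alongside the label in both VERDICT and CATCH: logit of the probability, hazard ratio per SD, with a prespecified non-linearity check such as a spline. Step 3 shows why a linear term alone may not be enough.
- Report the number labelled positive in each cohort.
- State which cut defines the label in the prognostic analysis, and whether calibration on CCTA changes it.

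The cost is small. The score already exists, no new data are needed, and the article describes validation in these cohorts as still planned. The drawbacks are one extra analysis and a hazard ratio per SD that is less direct for clinicians than a yes/no result. The label analysis stays for that purpose.

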### Ethical Considerations

This study is approved by the Danish National Committee on Health Research Ethics (1575037). All data used for algorithm development and validation were pseudonymized before research access.

The data were accessed for research purposes during the period from 2022 to 2023. We collected information on clinical indications for CT scans, radiographic diagnoses, and patient sex and age, with no other sensitive data obtained. Permission to use patient data was granted based on the determination that the study serves the public interest and only involves pseudonymized data. Therefore, the requirement for oral or written consent was waived. The validation cohorts were approved under separate ethical permissions and required written informed consent from all participants [7,23,24]. No compensation was provided to participants.

### Dissemination of Research Outcomes

Incidental findings are expected to be few due to the retrospective nature of the data collection as part of the clinical workflow; however, any findings identified during AI-assisted validation will be handled in accordance with the approved study protocol. Cases meeting predefined clinical significance criteria will be reviewed by a multidisciplinary safety committee and, if appropriate, communicated to the participant.

In terms of dissemination, the findings of this study are planned to be published in a high-impact, peer-reviewed journal and will be presented at international conferences, ensuring widespread dissemination and engagement with the broader scientific community (Multimedia Appendix 1). A separate technical methods article will be prepared and published independently. That methods article will provide a comprehensive and transparent description of the AI algorithm development, including data preprocessing, feature extraction, model training, and evaluation procedures (Multimedia Appendix 1).

### Data Management

All data are pseudonymized and stored securely on encrypted institutional servers with restricted access. Data extraction and coding are performed using automated scripts, with quality control checks applied during preprocessing.

### Statistical Analyses

In each validation cohort, the default thresholds obtained from the internal validation will be used to calculate the diagnostic ability of the AI algorithm to predict the prespecified heart and lung diseases. We will, for all diagnoses, calculate odds ratios, sensitivity, specificity, positive and negative predictive values, positive and negative likelihood ratios, and area under the curve from the ROC curves.

### Power Calculation

To account for variations in scanner generations, we included chest CT scans from all medical departments at a large hospital from 2016 onward, yielding approximately 5000 scans. Our initial estimation suggested the need for access to at least 15,000 scans to develop an algorithm with high diagnostic accuracy, as we expected that not all extracted scans would be suitable for algorithm development. Factors such as multiple scans per patient, incomplete thoracic coverage, and preprocessing challenges reduced the number of usable scans. Furthermore, we anticipated a distribution of diagnoses among patients with dyspnea, including heart failure, pneumonia, and chronic obstructive pulmonary disease exacerbations [9]. Given these considerations, we expect that our dataset of 5000 scans will provide a sufficient foundation for reliable training and validation of the AI model.

## Results

This is a retrospective study based on previously collected imaging data. As of August 2025, we have completed the extraction of CT scans and accompanying radiological reports. Natural language processing, CT segmentation, and the final stages of developing the AI algorithm are completed for pulmonary congestion but are still ongoing for the remaining conditions. The development and validation of the AI model constitute the main components of the study and are ongoing. Validation using 3 preexisting cohorts (FACTUAL, VERDICT, and CATCH) is planned (Multimedia Appendix 1). No new data collection or participant recruitment is planned, as all data have already been collected under previous ethics approvals.

A modified SPIRIT (Standard Protocol Items: Recommendations for Interventional Trials) schedule (Multimedia Appendix 1) outlines the timeline for key milestones, including algorithm development, internal validation, expert misclassification review, external validation in independent cohorts, and dissemination. We expect validation to conclude in late 2025, with final study results expected in 2026.

## Discussion

### Anticipated Findings

#### Overview

This study aims to develop and validate AI algorithms to automatically analyze chest CT scans and deliver instant feedback on the probability of dyspnea-related conditions. Our primary focus is on detecting cardiac decompensation while also laying the groundwork for assessing pneumonia and pulmonary embolism. To broadly test the algorithm, we evaluate the algorithm for cardiac decompensation in 3 different cohorts. The intended use of the algorithms is to assist in the detection of these conditions in a hospital setting, particularly in acutely admitted patients presenting with dyspnea. The algorithm is designed to support physicians, both radiologists and nonradiologists, by aiding in the early identification of critical findings while awaiting the final radiologic report. The AI model will provide interpretability through SHAP values for participant-level explanations, supported by visual inspection of segmentations and a numerical probability score for each detected disease. Its primary role will be to expedite early decision-making by highlighting relevant imaging features, potentially reducing time to diagnosis and treatment initiation. Optimizing the use of CT scans is crucial given their increasing prevalence. Currently, there is no standardized routine for describing cardiac decompensation on chest CT scans, presenting a gap that AI applications can fill.

#### AI Applications in Chest CT: Previous Evidence

CT scans are highly accurate for diagnosing cardiac decompensation and pulmonary diseases, often revealing subtle signs missed by chest radiographs [5,7]. Although CT scans involve higher radiation exposure, the advent of low-dose and ultra-low–dose chest CT scans has mitigated some of this concern while maintaining their diagnostic accuracy [25]. While it is unlikely to replace chest radiographs soon, CT imaging is frequently used when chest radiographs are inconclusive, especially in patients with undifferentiated dyspnea. It is important to address the upcoming challenges, including the shortage of radiologists and the need for AI assistance for nonradiologists. AI models can support physicians awaiting the final radiologic report and may alleviate radiologists’ workload, as AI models have been shown to reduce radiology reporting times by up to 22% [26].

To our knowledge, no published research has designed AI algorithms specifically to detect radiologic signs of cardiac decompensation on chest CT scans. One study demonstrated that machine learning–based quantification of lung water could identify increases in extracellular lung water in patients with heart failure with preserved ejection fraction, even in the absence of symptoms [27]. Previous research has highlighted the effectiveness of AI in diagnosing pulmonary conditions, including lung nodules [10], COVID-19, and COVID-19–related pneumonia [11,12]. A recent review emphasized that AI models can quantitatively assess pneumonia severity using CT images [13]. However, existing studies on CT imaging have primarily focused on patients with COVID-19. Our study extends this application, providing new insights into the use of AI for diagnosing different types of pneumonia. Limited research exists on AI and the detection of pulmonary embolism. One study demonstrated superior sensitivity and negative predictive values of AI models for pulmonary embolism detection, thereby reducing the risk of missed diagnoses [14]. Another study showed that an AI model aids detection and prioritization of incidental pulmonary embolisms on CT scans, but it was conducted in oncology patients [15].

Our study will assess the diagnostic efficacy of AI models in a broad population of hospital patients undergoing acute chest CT scans and across multiple diagnostic categories. For future clinical applications, the performance of the AI algorithms must be examined across various cohorts to demonstrate reliable differentiation between patients with and without critical conditions. At this stage, considerations such as diagnostic performance, regulatory approval, and integration into clinical workflow remain essential factors to establish the true clinical utility of these AI models.

#### Mitigating Imaging Variability and Validation Thresholds

Differences in imaging protocols across cohorts, including variations in scanner type, reconstruction kernels, and acquisition parameters, may affect AI model performance. To address this, the algorithm will be developed using data from multiple manufacturers, image types, and reconstruction kernels, and it will include both contrast-enhanced and noncontrast scans. This approach is designed to minimize the impact of technical variability and improve generalizability across different clinical settings, reducing the risk of bias from scanner settings and acquisition protocols. Planned cross-cohort validation will further ensure the robustness of the algorithm.

The sensitivity and specificity thresholds of 90% or greater chosen for validation are ambitious, but they align with performance levels generally regarded as necessary for clinical decision support in acute care, where the consequences of false negatives and false positives can be substantial. Thus, these thresholds serve as a target for ensuring patient safety and diagnostic reliability. We acknowledge that achieving such levels may involve trade-offs, including impaired sensitivity-specificity balance or reduced generalizability due to increased model complexity. High false positive rates could burden clinicians with unnecessary alerts, while false negatives might delay diagnosis of critical conditions.

